## Abstract

**Background:**

Second-generation drug-eluting stents (DES) have raised the bar of clinical performance. These stents are mostly made from cobalt chromium alloy. A newer generation DES has been developed from platinum chromium alloy, but clinical data regarding the efficacy and safety of the platinum chromium-based everolimus-eluting stent (PtCr-EES) is limited, with no comparison data against the cobalt chromium-based zotarolimus-eluting stent (CoCr-ZES). In addition, an antiplatelet regimen is an integral component of medical therapy after percutaneous coronary intervention (PCI). A 1-week duration of doubling the dose of clopidogrel (double-dose antiplatelet therapy (DDAT)) was shown to improve outcome at 1 month compared with conventional dose in acute coronary syndrome (ACS) patients undergoing PCI. However in Asia, including Korea, the addition of cilostazol (triplet antiplatelet therapy (TAT)) is used more commonly than doubling the dose of clopidogrel in high-risk patients.

**Methods:**

In the 'Harmonizing Optimal Strategy for Treatment of coronary artery stenosis - sAfety & effectiveneSS of drug-elUting stents & antiplatelet REgimen' (HOST-ASSURE) trial, approximately 3,750 patients are being prospectively and randomly assigned in a 2 × 2 factorial design according to the type of stent (PtCr-EES vs CoCr-ZES) and antiplatelet regimen (TAT vs DDAT). The first primary endpoint is target lesion failure at 1 year for the stent comparison, and the second primary endpoint is net clinical outcome at 1 month for comparison of antiplatelet therapy regimen.

**Discussion:**

The HOST-ASSURE trial is the largest study yet performed to directly compare the efficacy and safety of the PtCr-EES versus CoCr-ZES in an 'all-comers' population. In addition, this study will also compare the clinical outcome of TAT versus DDAT for 1-month post PCI.

**Trial registration:**

ClincalTrials.gov number NCT01267734.

## Background

Various second-generation drug-eluting stents (DES) have been developed in the hopes of improving both efficacy and safety compared with first-generation DES. Cumulative evidence is building suggesting that compared with the paclitaxel-eluting stent, the second-generation everolimus-eluting stent (EES; Xience V, Abbott Vascular, Santa Clara, CA, USA, Promus, Boston Scientific, Natick, MA, USA) is more effective and safe [1-3], and compared with the sirolimus-eluting stent, it has similar efficacy with a trend toward better safety [4-6]. The next addition to the second-generation DES market has been the zotarolimus-eluting stent (ZES; Resolute, Medtronic, Minneapolis, MN, USA), which showed equivalent outcome compared with the EES in the RESOLUTE All-Comers randomized trial [7]. Both EES and ZES are based on a cobalt chromium alloy stent. Most recently, a newly developed stent alloy, the platinum chromium alloy, was incorporated with everolimus to create the platinum chromium-based EES (PtCr-EES), the Promus Element stent (Boston Scientific, Natick, MA, USA). There are limited data on the clinical efficacy and safety of the PtCr-EES with only one modestly sized randomized trial that compared it against the cobalt chromium-based EES in a select group of patients and lesions [8]. In the current study, the PtCr-EES will be compared against the cobalt chromium-based ZES (CoCr-ZES) in a larger scale study with a broader all-comers population.

In addition, antiplatelet regimen is an integral component of medical therapy after percutaneous coronary intervention (PCI). In particular, inhibition of platelet reactivity in the first month post PCI is known to be critical in preventing thrombotic events, since higher on-treatment platelet reactivity is reported to be associated with higher risk of hard endpoints [9-12]. In the CURRENT-OASIS 7 trial, a 1-week duration of doubling the dose of clopidogrel was shown to improve outcome at 1 month compared with conventional dose in acute coronary syndrome (ACS) patients undergoing PCI [13]. In Asia including Korea, the addition of cilostazol as a third antiplatelet agent is used more commonly than doubling the dose of clopidogrel in high-risk patients. However, there has been no large-scale comparison of triple antiplatelet therapy (TAT) versus double-dose clopidogrel antiplatelet therapy (DDAT) to date.

## Methods

### Study objectives and hypotheses

The primary objective of the present study is to compare the efficacy and safety of coronary stenting with the PtCr-EES compared with the CoCr-ZES in the treatment of coronary stenosis, and to evaluate the efficacy and safety of a 1 month duration of TAT consisting of aspirin, clopidogrel 75 mg, and cilostazol 200 mg versus DDAT consisting of aspirin and clopidogrel 150 mg. The working hypothesis of this trial is that PtCr-EES is non-inferior to CoCr-ZES in prevention of target lesion failure (TLF) at 1-year post PCI, and TAT is non-inferior to DDAT regarding net clinical outcome, defined as a composite of cardiac death, non-fatal myocardial infarction (MI), stent thrombosis, stroke and PLATO ('PLATelet inhibition and patient Outcomes') major bleeding at 1 month [14].

### Study design

This is a prospective, randomized, single blind, blinded endpoint evaluation, multicenter trial with a 2 × 2 factorial design. The study algorithm is shown in Figure 1. After enrollment and index PCI procedure, clinical follow-up will occur at 1, 3, 12 months and yearly up to 3 years after intervention. Follow-ups will be conducted as telephone contacts or office visits. Unless clinically necessary, there will be no angiographic follow-up until 12 months post PCI, the timepoint for the primary endpoint of the stent comparison. In a subset of patients angiographic follow-up will be recommended at 13 months post PCI. In another subgroup of patients, clopidogrel on-treatment platelet reactivity will be measured using the VerifyNow P2Y12 assay at baseline PCI and at 1-month follow-up. This study is an investigator-initiated clinical trial with grant support from two sources, the Ministry of Health, Welfare, and Family Affairs of the Republic of Korea, and Boston Scientific Korea. Other than providing financial support, Boston Scientific was not involved with the protocol development or the study process, including site selection, management, and data collection and analysis. The authors are solely responsible for the design and conduct of this study, all study analyses, the drafting and editing of the paper and its final contents.

**Figure 1 F1:**
[figure not shown]
**Study algorithm**.

### Study population

Patients that are at least 18 years of age who show on coronary angiogram to have significant coronary artery or graft stenosis and meet all of the inclusion and exclusion criteria (Additional file 1: Table S1) are eligible for this study. This will be an 'all-comers' study, with no angiographic exclusion criteria in order to mimic real world clinical practice and will include the likes of multivessel stenting, left main stenting, chronic total occlusion intervention, bifurcation stenting, saphenous vein graft stenting, previous stent restenosis, and so on. The major exclusion criteria for study enrollment will be known hypersensitivity or contraindication to heparin, aspirin, clopidogrel, cilostazol, everolimus, zotarolimus, or contrast media, systemic (intravenous) us of everolimus or zotarolimus within 12 months, females of childbearing potential, unless a recent pregnancy test is negative, a history of bleeding diathesis, known coagulopathy (including heparin-induced thrombocytopenia), abnormal hemogram (hemoglobin < 10 g/dl or platelet count < 100,000 cells/μl) or will refuse blood transfusions, patients with severe left ventricular systolic dysfunction (left ventricular ejection fraction < 25%), those with cardiogenic shock, gastrointestinal or genitourinary bleeding within the prior 3 months, or major surgery within 2 months, and symptomatic heart failure. The patients that agree to participate in the study and give written informed consent, will be randomized 2:1 to either (a) PtCr-EES or (b) CoCr-ZES, and 1:1 to either (a) TAT or (b) DDAT (2 × 2 design). A total of 3,750 patients plan to be enrolled from 40 high-volume hospitals in Korea, the names and investigators of which are listed in Additional file 2: Appendix A.

### Interventions and study device, drug

PCI will be performed with the standard technique and device, that is, catheter, guidewire and balloon catheter. The decision to predilate the lesion, use glycoprotein IIb/IIIa inhibitors and dilate the stent adjunctively will be up to the operator's discretion. The Promus Element stent is available in diameters of 2.25, 2.5, 2.75, 3.0, 3.5 and 4.0 with lengths of 8, 12, 16, 20, 24, 28, 32, and 38 mm (32 and 38 mm lengths not available for 2.25 and 2.5 mm diameters). The Endeavor Resolute stent is available in diameters of 2.5, 2.75, 3.0, 3.5 and 4.0, with lengths of 12, 15, 18, 24, 30 and 38 mm (except for 2.5 mm stents which are available as 14 mm length instead of 15 mm, and 38 mm lengths not available for 2.5 and 2.75 mm diameters). It will be recommended that all diseased coronary or graft lesions that are the targets of intervention be fully covered by the stent, with non-diseased tissue at each end of the stent. In cases of long lesions that cannot be fully covered by one stent, stent overlap of approximately 1 mm to 4 mm will be recommended per manufacturer's instruction for use (IFU). It will be recommended that the allocated stent be implanted in all lesions treated in the same patient. However, other stents may be used in case of device failure, or situations where the operator decides that it is in the best interest of the patient to do so. The use of intravascular ultrasound (IVUS) or optical coherence tomography (OCT) to guide in the procedure will also be up to the operator's discretion.

All patients will receive approximately 300 to 600 mg of clopidogrel and 300 mg of aspirin loading before the procedure. The patients randomized to the TAT group will receive an additional loading of 200 mg cilostazol (Otsuka, Korea) followed by 100 mg twice a day maintenance. Those randomized to the DDAT group will receive 150 mg of clopidogrel maintenance.

### Outcome measures

There are two primary endpoints in this study. The primary endpoint of the trial for the stent comparison will be TLF, defined as a composite of cardiac death, target vessel-related non-fatal MI and ischemia-driven target lesion revascularization (TLR) at 12 months. The primary endpoint for the antiplatelet regimen comparison will be net clinical outcome, defined as a composite of cardiac death, non-fatal MI, stent thrombosis, stroke and PLATO major bleeding at 1 month [14]. The individual component definitions appear in Additional file 2: Appendix B. Stent thrombosis will be adjudicated according to the definitions of the Academic Research Consortium [15]. All endpoints will be analyzed principally on an intention-to-treat basis.

Secondary endpoints of the study will include all of the individual components of the primary endpoint. In addition, all death, ischemia-driven target vessel revascularization (TVR), target vessel failure (TVF), acute success (device, procedure) will be included as secondary endpoints. In the subgroup of patients that receive 13-month angiographic follow-up, both stents will also be analyzed using quantitative coronary angiography (QCA) for late luminal loss, percentage diameter stenosis, IVUS for percentage neointimal volume, or OCT for percentage neointimal coverage. In another subgroup of patients with on-treatment platelet reactivity (OPR) measurement, OPR will be compared between the two antiplatelet regimens, and according to genotype status. The effect of OPR on clinical outcome will also be analyzed.

### Statistical considerations

#### Sample size calculations

To test the first hypothesis that the PtCr-EES is non-inferior to CoCr-ZES in reducing 12-month cumulative TLF after PCI, we assumed the TLF rate of PtCr-EES and CoCr-ZES to be 6.5%, based on the results from previous randomized trials [1,2,7]. Using a non-inferiority log-rank design with a non-inferiority margin of hazard ratio 1.5, sampling ratio of EES:ZES at 2:1, allowing 5% attrition rate for the 12 months, a total of 3,750 patients would result in a power of at least 80% power with an one-sided α of 2.5%.

Also, to test the second hypothesis that TAT is non-inferior to DDAT regarding 1-month net clinical outcome, we assumed the net clinical outcome rate of TAT and DDAT to be 2.0% and 3.0%, respectively. The net clinical outcome is defined as a composite of cardiac death, non-fatal MI, stent thrombosis, stroke and PLATO major bleeding at 1 month. With a non-inferiority design, a non-inferiority margin of 0.75%, 1:1 randomization to either groups and allowing for 2.5% attrition for 1-month clinical follow-up, a total of 3,750 patients would provide a one-sided α of 2.5% and > 90% power.

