## Discussion

### EES and ZES in clinical practice

The second-generation CoCr-EES (Xience V, Promus) has been shown to be either comparable or better than its first-generation counterparts. In large scale randomized trials against paclitaxel-eluting stents (PES), such as the SPIRIT IV and COMPARE trials, it was superior to PES with regard to both efficacy and safety where the primary clinical endpoints were reduced by 38% and 31%, respectively [1,2], which has now been reaffirmed in a meta-analysis [16]. In randomized trials and meta-analysis comparing CoCr-EES and SES, such as the EXCELLENT, ISAR-TEST 4, SORT-OUT IV, and so on, CoCr-EES showed similar efficacy with slight trend toward superior safety [4-6]. The next addition to the second-generation DES market has been the CoCr-ZES (Endeavor Resolute), which showed equivalent outcome compared with the CoCr-EES in the RESOLUTE All-Comers randomized trial [7]. Because of the all-comers population that was studied in this trial, data were available regarding to the performance of the second-generation stents in complex lesions such as coronary total occlusions, bifurcation lesions, saphenous vein grafts, in-stent restenosis, unprotected left main lesions, multivessel stenting, and so on, which constituted approximately two-thirds of the lesions treated in the trial [17]. In this complex subgroup, there were no significant differences between the two DES devices but the TLF rate at 1 year numerically favored CoCr-ZES. Both of these second-generation DES are based on a cobalt chromium alloy stent. Most recently, a newly developed stent alloy, the platinum chromium alloy, was incorporated with everolimus to create the PtCr-EES, the Promus Element stent (Boston Scientific). In the only randomized trial to date with the PtCr-EES, the PLATINUM trial, where it was compared against CoCr-EES in a select group of patients with various angiographic exclusions [8], PtCr-EES was non-inferior to CoCr-EES for the primary endpoint of TLF, with insignificant differences in measures of safety and efficacy through 1 year. Both stents showed low event rates at 1 year (TLF rate: 3.4% vs 2.9% for PtCr-EES vs CoCr-EES, *P *= 0.60). However the PtCr-EES has not been studied randomly in a broader population of patients as was enrolled in the RESOLUTE All-Comers trial, which better reflects the day-to-day clinical practice in most centers of coronary intervention. The non-inferiority margin of 3.25% may seem large given that the estimated rate of the primary endpoint is 6.5%. However, in the RESOLUTE All-Comers trial and the PLATINUM trial, well known previous studies incorporating the non-inferiority design regarding stent comparisons, a non-inferiority margin of 3.5% has been used [7,8]. In addition, because of the paucity of the data on PtCr-EES, the sampling ratio was set at 2:1 to maximize the number of patients randomized to the PtCr-EES arm.

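### The stent non-inferiority margin is a hazard ratio of 1.5 in the sample-size section but 3.25% in the Discussion; these are different criteria, and the same data can give opposite decisions in either direction.

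*Protocol article*

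**What the plan says.** Sample size calculations (Protocol article) sets the margin for 12-month target lesion failure (TLF) on the hazard-ratio scale: "Using a non-inferiority log-rank design with a non-inferiority margin of hazard ratio 1.5". The other inputs there are equal event rates ("we assumed the TLF rate of PtCr-EES and CoCr-ZES to be 6.5" per cent), "sampling ratio of EES:ZES at 2:1", "allowing 5% attrition rate for the 12 months", and a one-sided α of 2.5%. The result given is that "a total of 3,750 patients would result in a power of at least 80% power".

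The Discussion, under EES and ZES in clinical practice, describes the margin of the same comparison differently: "The non-inferiority margin of 3.25% may seem large given that the estimated rate of the primary endpoint is 6.5" per cent. It defends that size by noting that in two well-known stent trials "a non-inferiority margin of 3.5% has been used". Set against an event rate and against other percentage margins, 3.25% reads as an absolute difference in TLF rates.

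Statistical analyses says that Kaplan-Meier event rates will be compared with the log-rank test and that the null hypothesis will be evaluated by non-inferiority statistics. It repeats neither margin and names no scale for the decision.

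**The concern.** One primary endpoint carries two thresholds on two scales, and nothing in the article calls one a translation of the other. The analysis section does not settle the matter: comparing Kaplan-Meier rates suggests a risk difference, while the log-rank test suggests a hazard ratio. A hazard-ratio margin keeps the tolerated relative excess constant and lets the absolute excess move with the event rate; an absolute margin does the opposite. The two can agree at only one control rate.

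At stake is the declaration of non-inferiority itself. In addition, the article's only argument for the size of the margin is made for the percentage version, while the sample size and power rest on the hazard ratio.

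**Working it through.** **Inputs.** From Sample size calculations: N = 3,750, 5% attrition, 2:1 EES:ZES, 6.5% TLF in both arms, one-sided α 2.5%, HR margin 1.5. From the Discussion: margin 3.25%. Evaluable patients: 3,750 x 0.95 = 3,562.5, that is 2,375 EES and 1,187.5 ZES.

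**1. The plan's own power (HR 1.5, Schoenfeld).**
- Events = 3,562.5 x 0.065 = 231.6.
- Power = Φ(√(231.6 x 2/3 x 1/3) x ln 1.5 − 1.96) = Φ(2.909 − 1.96) = 82.9%.
- 80% power needs 215 events: 215 / 0.065 = 3,308 evaluable patients, or 3,483 after dividing by 0.95.

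The stated power of at least 80% is reproduced.

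**2. The same N under 3.25 points absolute.**
- SE = √(0.065 x 0.935 x (1/2,375 + 1/1,187.5)) = 0.00876.
- Power = Φ(0.0325 / 0.00876 − 1.96) = Φ(3.709 − 1.96) = 96.0%.
- 80% power would need 2,034 evaluable patients, or 2,142 with attrition.

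So 3,750 patients at about 80% power matches the HR criterion, not the absolute one.

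**3. Converting between the margins** (p_EES = 1 − (1 − p_ZES)^1.5, and HR = ln(1 − p_EES) / ln(1 − p_ZES)).
- 0.5 x 6.5% = 3.25%: the ratio 1.5 applied to the risk.
- HR 1.5 at 6.5%: 1 − 0.935^1.5 = 9.59%, a difference of 3.09 points.
- 3.25 points at 6.5%: ln(0.9025) / ln(0.935) = 1.526.

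| ZES rate | HR 1.5 in points | 3.25 points as HR |
|---|---|---|
| 3.0% | 1.47 | 2.12 |
| 6.5% | 3.09 | 1.53 |
| about 6.9% | 3.25 | 1.50 |
| 10.0% | 4.62 | 1.35 |

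**4. Power with equal true rates.**

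| TLF rate | HR 1.5 | 3.25 points |
|---|---|---|
| 3.0% | 51% | >99.9% |
| 6.5% | 83% | 96% |
| 8.0% | 90% | 92% |
| 10.0% | 95% | 86% |

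The two powers cross at about 8.4%.

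**5. Decisions on hypothetical observed rates.** Upper limit for the difference: d + 1.96 x √(p_E(1−p_E)/2,375 + p_Z(1−p_Z)/1,187.5). Upper limit for the HR: HR x exp(1.96 x √(1/events_E + 1/events_Z)).
- *EES 7.5%, ZES 6.5%.* Difference: 1.00 + 1.96 x 0.897 = 2.76 points, passes 3.25. HR: 1.160 x exp(1.96 x 0.1363) = 1.515, fails 1.5.
- *EES 11.2%, ZES 10.0%.* Difference: 1.20 + 1.96 x 1.085 = 3.33 points, fails 3.25. HR: 1.127 x exp(1.96 x 0.1104) = 1.40, passes 1.5.

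The decisions conflict near the planning rate and again above it, in opposite directions.

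**The case against.** The best defence is that the article has only one statistical specification. Methods gives HR 1.5 within a log-rank design, the stated power agrees with it, and the analysis section names the log-rank test. The 3.25% appears only in the Discussion, where the size of the margin is being put in context, and as half of 6.5% it is most naturally HR 1.5 restated at the planning rate. The discrepancy there is small: 3.09 against 3.25 points. Much of this stands. It makes HR 1.5 the better-supported reading, but the text does not label the percentage as approximate, and step 5 shows that the decision can turn on which is used.

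The gap of 83% versus 96% power should also be read with care. Testing HR 1.526, the exact equivalent of 3.25 points at 6.5%, would have about 86% power. So only about 3 of the 13 points come from the size of the margin; the rest come from testing on a difference scale instead of a log hazard-ratio scale. This is a reason to fix the scale as well as the number.

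A reader might infer three stronger things that the article does not support:

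- *That HR 1.5 is always the stricter criterion.* It is not. As margins the two coincide at a control rate of about 6.9%, and the power ordering reverses at about 8.4%.
- *That the margin was left open to be chosen once the event rate was known.* Recruitment was complete at publication, but the full protocol is not shown and may fix the criterion. A success rule absent from a condensed article is no fault in itself; the contradiction between two stated margins is.
- *That the trial will run near 3% TLF, where 3.25 points would allow about a doubling.* The 3.4% and 2.9% rates in the Discussion come from a trial that it describes as having a selected population with angiographic exclusions. This trial has no angiographic exclusions and plans for 6.5%. The 3% rows show the range and are not a forecast.

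**Conclusion.** The point holds as a contradiction in the decision threshold of a primary endpoint. Methods and Discussion state different margins on different scales, and the analysis section does not reconcile them. At the planning rate the margins lie 0.16 points apart (3.25 − 3.09), but power differs by about 13 percentage points, and plausible results can pass one and fail the other in either direction. The stated power belongs to HR 1.5.

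The sample size is not in error: 82.9% satisfies the claim of at least 80%.

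The figures assume that 3.25% means percentage points, that the 5% attrition simply removes patients, and that hazards are proportional in the conversions. They use the Schoenfeld formula for the HR power, a normal approximation for the difference, and the simple event-count standard error for the log HR. The observed rates in step 5 are hypothetical. Close cases such as 1.515 against 1.5 could shift slightly under another method; the divergence of the two criteria would not.

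**What to change.** Before database lock, state one decision rule in both Sample size calculations and Statistical analyses: PtCr-EES is non-inferior if the upper one-sided 97.5% confidence limit for the EES:ZES hazard ratio for 12-month TLF is below 1.5. This is the margin that the log-rank design and the stated power rest on. If the full protocol had pre-specified a different criterion, that one should be stated instead, with its own power.

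In the Discussion, replace the 3.25% by *HR 1.5, about 3.1 percentage points at a 6.5% control rate*. The 3.5% margins of the earlier trials can stay as context, but not as direct support for a hazard-ratio margin. Report the absolute difference in TLF with its confidence interval descriptively.

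The cost is wording only. The sponsor gives up the absolute margin, which is the more lenient one near and below the planning rate. No change to the sample size is needed.
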